#### Structured Observation Tasks

Parents and toddlers entered a room with a camera set up and a one-way mirror. The assessment began with a free play task without toys (5 min), followed by free play with a doll’s house/furniture, a toy car and toy family members (5 min). Parents were then asked to complete a semi-structured story telling task using a doll’s house where parents were given instructions to use the play equipment to tell a story with four different events where the: parents go away overnight leaving children in care of a trusted adult; children have a fight; the family dog runs away; and the parents return the next day (Cervantes and Callanan, 1998). Next parent and toddler selected two emotion faces (from a selection of five faces of toddlers expressing different emotions) and were asked to discuss a time when the child had felt this way. Then, a frustration task was given where a desirable toy in a plastic see-through bag was placed in front of the child and the parent was instructed to fill in a questionnaire before the child could open the desirable toy. The child was given three simple wooden blocks to play with while waiting. Once the parent completed the questionnaire, the toddler could play with the toy for 5 min before they were asked to pack up.

#### Coders and Training

Coding will be carried out by undergraduate and graduate psychology students external to the study and blind to participant intervention status. All students will participate in 2 days of training. Interrater coding will be completed with the first and second author until student coding is moderate to high in terms of interrater reliability. During coding students will have regular supervision to maximize interrater reliability and address difficulties with coding. Interrater reliability will be conducted with 10% of all observation assessments.

### Stress Cortisol

Cortisol in hair samples will be collected to measure parent and toddler stress as a secondary outcome. To use a physiological measure to assess parental and toddler stress levels, hair cortisol assays using hair cut from the head will be collected from parents and toddlers at the time of the observation assessment. This technique has been validated in human studies and has also been found to be a marker of chronic systemic stress (Russell et al., 2012). With hair growing at approximately one centimeter/month, the first centimeter of hair from the scalp can be measured to determine the previous months’ cortisol production.

Following a written protocol, researchers cut a sample of hair approximately 3 mm in width from the back of the parent and toddler’s head as close to the scalp as possible. Samples will then be tied using cotton and packaged in foil for storage at room temperature. Analysis will be conducted by an external laboratory, Stratech Scientific. Analysis involves removal of surface contaminants by washing samples with isopropanol for 3 min on a rotor then left to dry in a clean protected hood for 4 days. Hair will then be stretched out and 1 cm of hair (25–40 mg, representing cortisol levels during the last month) will be cut from the scalp end and ground to a fine powder. Steroids will be extracted with methanol. The extracted slurry will be centrifuged at high speed to pellet hair particles and clear methanol containing extracted steroids will then be transferred to a clean tube and evaporated. Assay diluent buffer will be placed in each tube, vortexed and left to stand then vortexed again. To optimize accuracy each sample analysis will be duplicated. Cortisol will be quantified using ELISA kits (Salimetrics, United States). Intra assay variability will be reported at 5.1% and inter assay variability at 5.8%. Data will be provided as nanograms of cortisol per 50 mg of hair.

### Power Analyses

Using methods proposed by Eldridge et al. (2006), the estimated design effect for the study is 1.30 (based on 40 clusters of average size 7, a coefficient of variation for cluster size of 0.25, and a conservative at worst intra-class correlation of 0.05). The following power calculation incorporates this estimated design effect from clustering, and is done for feasible differential treatment effects at 15 months follow-up, where attrition will be highest. The treatment effect difference is conservatively estimated to result in group differences of about 0.40 SDs for continuous outcome measures. To achieve 80% power at a 5% significance, the required sample size at follow-up needs to be 100 × 1.30 = 130 participants in each condition. Based on our other studies, including our pilot study, we estimated there will be 10% attrition. This implies that 130/0.90 = 144 participants are needed in each condition for the study to have sufficient power.

### Planned Statistical Analyses

Data will be analyzed using SPSS, beginning with data cleaning and assumption testing. Multiple imputation will be used to address missing data. A series of analyses are planned. First, independent samples *t*-test analyses will determine whether there are any systematic differences between pre-intervention scores for demographic and outcome variables for the intervention and the control conditions. Any baseline differences will be used as covariates in subsequent analyses. In addition, those with missing time 2 and 3 data points will be examined to determine differences from those completing follow-up assessment. Next, because parents are nested in centers, intraclass correlations will be computed to assess if center membership contributes to outcome variance. Our previous work has shown that kindergarten or school membership contributes from 8 to 11% of variance in child outcome variables (e.g., [name] et al., 2010; Wilson et al., 2012). Therefore, multilevel analyses using the mixed procedure in SPSS will be conducted to compare intervention and control participants across the different measures over time whilst considering the impact of the nested design (i.e., children attending different child care centers) and baseline covariates. Effect sizes will be calculated using Cohen’s *d*.

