### Aims and Hypotheses

This paper outlines the research protocol and recruitment process being used to evaluate the efficacy of TOTS. This paper also describes the process of recruitment being used to obtain the sample while outlining strategies used to overcome barriers to engaging parents of young children in a parenting intervention. The primary outcome is change on the measures of parent emotion socialization, and the secondary outcomes are change on the measures of parent functioning (emotion regulation and mental health), toddler’s social, behavioral and emotional functioning, and systemic cortisol stress in parents and toddlers. It is hypothesized that based on the TOTS pilot study (Lauw et al., 2014), at 15-month follow-up we will see improved parent emotion socialization (reduced emotion dismissiveness and increased emotion coaching) in intervention participants but not control participants. It is also hypothesized that at 15-month follow-up we will see improved parent functioning (reduced emotion regulation difficulties, improved parent mental health) and reduced child behavior problems in intervention participants but not control participants. The impact of the program has not previously been examined with cortisol stress, however, if parents improve in skills regulating their own emotions and their responses to their toddler’s emotions after program participation, it is hypothesized that at 15-month follow-up there will be lower cortisol stress for parents and toddlers in the intervention condition (but not control).

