### Toddler Functioning

Toddler behavior was measured as a secondary outcome, while toddler temperament and developmental status were measured as possible confounding factors.

*Brief Infant-Toddler Social Emotional Assessment* (BITSEA; Briggs-Gowan et al., 2002) – Toddler social-emotional/behavioral problems were measured using the BITSEA, a 34-item parent-report measure which assesses toddler behavior problems occurring in the past 4 weeks. Items (e.g., *Is restless and can’t sit still*) are rated from 1 (*not true/rarely*) to 3 (*very true/often*) and measures internalizing problems (e.g., *seems nervous, tense or fearful*, or *worries a lot*), externalizing problems (e.g., *hits/shoves, kicks or bites children*, or *cries or tantrums until exhausted*), and dysregulation problems (e.g., *has trouble falling asleep*, or *gags or chokes on food*). The measure has demonstrated excellent test–retest reliability, good interrater agreement across parents and carers with this age group (Briggs-Gowan et al., 2004; Zimmer-Gembeck and Thomas, 2010), and has been used in an Australian context (e.g., Zimmer-Gembeck and Thomas, 2010). Briggs-Gowan et al. (2004) report Cronbach’s alpha for this subscale as 0.79 for parent ratings. In the current sample, Cronbach’s alpha at baseline for the total score was 0.74.

*Toddler Temperament Scale* (TTS) – Toddler temperament was measured using the *Short Infant Toddler Temperament Questionnaire*, developed by the Australian Temperament Project (ATP; Prior et al., 1989). This parent-reported scale consists of 13 items and captures three dimensions of temperament (Approach, Reactivity, and Persistence), giving a subscale for each, as well as a total score. Parents report the frequency with which their toddler, e.g., *smiles when an unfamiliar adult plays with him/her* (Approach), *responds to frustration intensely (screams, yells)*, (Reactivity), and *stops to examine objects thoroughly (5 min or more)* (Persistence), on a six-point Likert scale from *almost never* to *almost always*. A TTS total score was computed to reflect a more difficult temperament (higher score) using Reactivity and reverse scoring Approach and Persistence. The TTS has demonstrated satisfactory reliability and validity and has been used widely in Australia (e.g., Pedlow et al., 1993). In the current study, Cronbach’s alpha for the total difficulty scale at baseline was 0.67.

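### Covariates are picked by baseline t-tests that ignore centre clustering, so the adjusted model hangs on chance imbalance; it should be fixed in advance and include each outcome's baseline score

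*Protocol article*

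**What the plan says.** Under Planned Statistical Analyses, the protocol article gives a sequence of steps. The opening step reads: "First, independent samples *t*-test analyses will determine whether there are any systematic differences". The variables tested are the "pre-intervention scores for demographic and outcome variables for the intervention and the control conditions". The rule that follows is: "Any baseline differences will be used as covariates in subsequent analyses". No threshold for a difference is given.

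Clustering comes in only afterwards: "Next, because parents are nested in centers, intraclass correlations will be computed to assess if center membership contributes to outcome variance". A mixed model is then planned to "compare intervention and control participants across the different measures over time whilst considering the impact of the nested design", together with baseline covariates. The t-test screen is the only rule in the document for choosing those covariates.

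Three other places bear on the point:
- Aims and Hypotheses: "The primary outcome is change on the measures of parent emotion socialization".
- Toddler Functioning: "toddler temperament and developmental status were measured as possible confounding factors".
- Randomization Procedure: centres were paired on local median house price and on the number of parents who had completed baseline questionnaires. Neither pairing variable is named in the model.

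**The concern.** Parents learned their condition only after the baseline assessment, so among the 322 parents enrolled and allocated a baseline difference between arms is chance. A significance test of such a difference says nothing about whether the variable predicts the outcome, and prediction is what makes a covariate worth including. The rule therefore admits variables because they happened to differ and passes over prognostic ones because they did not.

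The test used is also the wrong one for this design. It treats parents as independent, while the same section goes on to allow for correlation within centres, so it calls differences significant more often than its nominal level.

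At stake is whether the adjusted model is known before the data are seen and is the same for every outcome, and whether the trial uses the precision that its baseline data offer.

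**Working it through.** **The plan's own figure.** Power Analyses gives 40 clusters, mean size 7, coefficient of variation of cluster size 0.25, ICC 0.05 and a design effect of 1.30.
- Simple form: 1 + (7 − 1) × 0.05 = 1.30, as stated.
- With the stated coefficient of variation: 1 + ((0.25² + 1) × 7 − 1) × 0.05 = 1.32. This form is used below.

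**How often the screen flags a variable with no true difference.** A test that ignores clustering uses a standard error too small by √DE (DE = design effect). Its real level, taking 5% two-sided as nominal, is 2(1 − Φ(1.96/√DE)).
- ICC 0.05: DE 1.32, level 8.8%.
- ICC 0.08: DE 1.515, level 11.1%.
- ICC 0.11: DE 1.708, level 13.4%.

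The values 0.08 and 0.11 are the 8 to 11% of variance that the protocol reports for child outcomes in earlier trials. A simulation with 40 unpaired centres gave 7.6–9.0% at ICC 0.05 and 11–13% at ICC 0.10.

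**How many covariates enter by chance.** The number of variables tested is not stated. For an assumed 20, the expected number flagged is 20 × 0.088 = 1.8 at ICC 0.05 and 20 × 0.134 = 2.7 at ICC 0.11. A valid 5% test would flag 1.0. If the 20 were independent, the chance of at least one would be 84% and 94%, against 64% for a valid test.

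**What the screen does not secure.** The baseline score of a given outcome becomes a covariate only if flagged, so it is not selected in about 87–91% of trials. Centre type and the pairing variables have no fixed place, and child age enters only if it differs. Temperament and developmental status are neither demographic nor outcome variables, so the screen as worded does not reach them.

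**Effect on the error rate.** This depends on the form of the model.
- *Model of the 15-month score.* Simulation (40 unpaired centres, mean size about 6.5, 2,500 runs per setting, correlation 0.7): with no true effect, adjusting for baseline only when flagged rejected in 3.0% of trials at ICC 0.05 and 2.2% at ICC 0.10. Always adjusting gave 5.0% and 4.4%. At a true 0.40 SD and ICC 0.05, power was 82% with the selection rule, 97% with fixed adjustment and 79% with none.
- *Arm × time model.* With complete data at two times and a common within-parent correlation, the contrast is built from within-parent differences. A covariate entered as a main effect is constant over time and cancels. Selection then changes the contrast little unless covariate × time terms are added, and none is mentioned.

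**Precision available.** Let r be the correlation between baseline and 15-month scores. The documents do not give it, so a range is assumed. Relative to an unadjusted 15-month comparison, variance is 2(1 − r) for change and 1 − r² with baseline as covariate; their ratio is (1 + r)/2.
- r = 0.5: change 1.00, adjusted 0.75, ratio 0.75.
- r = 0.6: change 0.80, adjusted 0.64, ratio 0.80.
- r = 0.7: change 0.60, adjusted 0.51, ratio 0.85.

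Since 1/0.85 = 1.18 and 1/0.75 = 1.33, the gain over a change analysis equals 18–33% more participants. At the plan's effective size of 100 per arm and 0.40 SD, power is 90%, 94% and 98% adjusted, against 81%, 89% and 95% for change.

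**The case against.** The strongest reply is that the planned model runs over time and the primary outcome is change. Baseline is then probably already in the model as a response, and a selected covariate hardly moves the treatment contrast. This stands, and it limits the harm. A reader might infer from the t-test rule that baseline scores are ignored or that false positives rise. The documents support neither: the over-time wording makes the first unlikely, and the error rate is conservative in a 15-month model and little changed in an arm × time model.

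It can also be said that the precision gain is a preference for baseline adjustment over change scores, resting on an assumed correlation and on individual-level formulas. That is fair. The gain is an available improvement, not a consequence of the t-test sentence alone.

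Matching on house price and uptake may reduce chance imbalance on related variables and so offset part of the excess flagging. The calculations and simulation ignore matching, so the 9–13% are figures before that offset.

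Not every difference in the analysed sample need be chance. Results reports that 14 of 180 intervention parents (7.8%) and 2 of 142 control parents (1.4%) left after baseline, giving the final 306. Differences there may partly reflect unequal withdrawal. That qualifies the statement about chance, but it does not make t-test selection a remedy.

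A reader might also think that the rule discards temperament for failing to differ. It does not, because temperament is outside the variables tested.

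**Conclusion.** The point holds in a limited form. The protocol states a data-driven covariate rule based on tests that ignore clustering. They flag about 9% of null variables at ICC 0.05 and about 11–13% at 0.08–0.11, taking a 5% threshold and no offset from matching. The adjusted model is therefore not fixed in advance, can differ between outcomes, and does not guarantee a place for any prognostic variable.

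The cost is an unfixed model and forgone precision: a variance ratio of 0.75–0.85 against a change contrast, for an assumed correlation of 0.5–0.7. It is not an inflated type I error. Nor does this point show that the trial is underpowered: the sample size calculation assumes no covariate adjustment and reproduces to within about 3%. The change is worth making because it costs nothing.

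**What to change.** Delete the t-test selection rule and report baseline characteristics by arm descriptively. For every outcome, pre-specify one clustered model of either form:
- the 15-month score on arm, the same measure's baseline score and a short fixed list of covariates already collected, for example child age, centre type and the house-price matching variable; or
- a repeated-measures model with the baseline means constrained to be equal between arms.

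State the list before outcome data are examined, and keep it whatever the baseline comparison shows. If temperament and developmental status are to be adjusted for as possible confounders, name them in the list.

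Include matching pair as a term only if one centre of each pair went to each arm. Study Design and Randomization Procedure can both be read as allocating whole pairs to one condition. Pair fixed effects would then be collinear with arm and the treatment effect could not be estimated, so the wording should be clarified first.

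The cost is a change to the analysis text. No new data are needed.

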## Results

A total of 470 parents of toddlers expressed interest in participating in the study (see Figure 1, participant flow). An exact percentage uptake rate was difficult to determine for MCH centers because advertising was on the walls of centers and it was not possible to determine the number of times the nurses offered the program to parents. However, CC centers had an average of 65 toddlers per center – resulting in a 4.6% uptake. Parents had heard about the study via CC (*n* = 321), MCH (*n* = 113) centers, or other participating parents (*n* = 36; note that these were enrolled only if their center was participating in the study). Of the 470 parents, 58 participants were not eligible to take part, and 90 parents withdrew their interest from the study, leaving a total of 322 parents who completed their baseline questionnaire and were enrolled in the study (68.5%). Of the 58 participants who were not eligible to take part, 27 parents had children not within the specified age range (too old *n* = 19; too young *n* = 8), 22 parents were unable to attend the designated group (due to location or times not suitable *n* = 17, moving away *n* = 4, or taking a long vacation *n* = 1), two parents had insufficient English, and one parent was the ex-partner of a parent in the study. Three parents’ centers were not part of the study, and three parents expressed interest after their center was matched and randomized and so were not included in the final sample. All parents not eligible were offered referrals to other parenting programs. Of the 70 parents who did not go ahead with participating after expressing interest, the majority withdrew their interest because they were too busy (*n* = 22) or the time commitment was too great (*n* = 7). Other reasons for not going ahead with the study were child care issues (*n* = 5), health reasons (*n* = 4), needing immediate support (*n* = 1), deciding they no longer needed parenting help (*n* = 1), and wanting to do a different program (*n* = 2). Thirteen parents did not provide a reason for withdrawing after expressing interest, and 35 parents did not respond to calls or emails.

Three hundred and twenty-two participants completed baseline questionnaires with 180 in the intervention condition and 142 allocated to the waitlist control condition. Of the 322 enrolled participants, 16 parents withdrew after completion of their baseline data. Of these, two were waitlist control parents (one did not wish to wait 15 months; the other had conflicting commitments in 15 months). Of the 14 intervention parents, two were excluded because they were assessed to be ineligible (e.g., not suitable for the parenting program due to high social anxiety *n* = 1; child too young *n* = 1). Seven parents did not attend any sessions (baby too unsettled *n* = 1, child care arrangements did not work out *n* = 3, unforeseen traumatic event *n* = 1, other commitments *n* = 2). Two intervention parents found the observation assessments stressful and did not wish to participate in the intervention. A scheduled daytime group did not go ahead due to low numbers and three of these participants were unable to attend an evening session. Instead they were sent a DVD and program booklet and were offered the program at a future date.

The final sample was 306 participants (166 intervention and 140 waitlist control), of which 241 were recruited from CC and 65 from MCH centers. Observation assessments were conducted with a random selection of 246 parent–child dyads at baseline (as mentioned earlier this was due to funding constraints). Hair cortisol concentration data was collected for 235 parents who attended the assessments and for 201 toddlers at baseline. Hair samples were not taken from 11 parents due to them choosing not to give a hair sample and from 34 toddlers due to parents not wishing the hair sample to be taken or due to toddler’s being distressed at receiving a haircut (some had never had a haircut before). There were no significant differences between those participants who completed the questionnaires only and those who completed the full assessment battery (including questionnaires, parent–child assessment and cortisol stress measures).

Participants were 272 mothers (88.9%), one kinship caring grandmother (0.3%), and 33 fathers (10.8%) with a mean age of 37.1 years (*SD* = 4.9; range = 16.9–70.1 years) of a toddler aged on average 25.6 months (*SD* = 5.3; age range = 17.2–36.4 months; males *n* = 176; 54.6%). The majority of participants had either one (*n* = 176; 57%) or two children (*n* = 115; 37%; range = 1–5 children), and resided with their child and the child’s other parent (*n* = 270; 88.2%), while six parents had re-partnered (2%), 24 (7.8%) were sole parents, and six lived in shared custody arrangements (2%). English was the main language spoken at home (93.1%), with 224 participants (73.2%) born in Australia, and the remainder born in North America/New Zealand/United Kingdom/Europe (39 participants; 12.7%) or Asia/Africa/Middle East (29 participants; 9.5%). High school completion rate was 95.4%, and most parents reported completing a post-school qualification (96.4%; none = 3.6%; certificate/trade = 5.6%; diploma = 5.9%; undergraduate degree = 39.5%; higher degree/diploma = 44.2%). Two hundred and thirty-two parents (76.1%) were employed (77.8%), working an average of 26.8 h per week (*SD* = 10.02; range 2–50 h per week), and five parents (1.6%) were on maternity leave. Occupations were mainly managerial or professional (56.9%), but also included associate professionals (9.5%), clerical/sales/transport workers (8.1%) and tradespersons (1.3%). Seventy-three participants (23.9%) did not provide details about their occupation. Few families (5.6%) were below the Australian poverty threshold of AUD $49,972 per year for couples with two children (Melbourne Institute of Applied Economic and Social Research, 2015). More specifically, 37 parents (12.1%) reported low gross annual family income ($0–64,999), 86 parents (28.1%) reported middle-incomes ($65,000–119,999), and 183 (59.8%) reported higher incomes (>$120,000). In 2016, the median household income for Melbourne was $95,000 (Australian Bureau of Statistics, 2016).

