### Strengths and Limitations

This study is innovative in targeting parents when their children are young and addressing emotion socialization processes rather than behavioral methods of parenting. The study will follow the CONSORT guidelines for intervention evaluation (Schulz et al., 2010) and will use mixed methods of evaluation (parent-report, parent–child observation, physiological measures of systemic cortisol in parent/toddler) in order provide detailed analysis of the potential impact of the intervention on primary and secondary outcomes and to reduce expectancy bias that can occur by using parent report alone. Cluster randomization of centers not individuals enabled snowballing/social media to increase recruitment in any particular center while ensuring that condition assignment was unknown to participants and the research team during recruitment. Cluster randomization also enables the effect of centers to be taken into account in statistical analyses by computing intra-class correlations and including these in multilevel analyses of outcomes. Immediate and long-term follow-up of 12 months post intervention (15 months from baseline) will be used for examining changes over time and whether the intervention achieves the intended primary and secondary outcomes of improving parenting, parent functioning, and children’s wellbeing. Measures of implementation quality, including fidelity of intervention delivery and post-intervention satisfaction by parents will enable detailed information to be collected about the intervention and potential barriers to retention.

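### Sixteen parents lost after allocation (14 of 180 intervention, 2 of 142 control) are left out of the final sample of 306, and most of the intervention losses concern uptake or delivery of the programme

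*Protocol article*

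**What the plan says.** All places are in the protocol article. The Results describe 322 parents who enrolled by completing the baseline questionnaire, "with 180 in the intervention condition and 142 allocated to the waitlist control condition". They continue: "Of the 322 enrolled participants, 16 parents withdrew after completion of their baseline data". On the control side, "two were waitlist control parents (one did not wish to wait 15 months; the other had conflicting commitments in 15 months". On the intervention side the reasons are:

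- Two were judged not eligible: "Of the 14 intervention parents, two were excluded because they were assessed to be ineligible". One had high social anxiety and the other had a child who was too young.
- "Seven parents did not attend any sessions".
- Two found the observation assessment stressful and did not want the programme.
- Three could not switch to an evening session when a daytime group was cancelled for low numbers. They were sent a DVD and booklet and offered the programme later.

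The Results then conclude: "The final sample was 306 participants (166 intervention and 140 waitlist control".

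The abstract and Trial Status give 306 as the number recruited, and the abstract adds that these 306 completed the baseline questionnaires. Planned Statistical Analyses provides for multiple imputation and multilevel models but names no analysis set. Inclusion/Exclusion Criteria lists one exclusion, insufficient English. Randomization Procedure says that centres were paired partly on the number of parents who had completed baseline, and that parents learned their condition after the baseline assessment.

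**The concern.** Centres were paired on counts of parents who had already completed the questionnaire, so the 322 are the parents whose centres were randomised. The 16 left the sample after that point, and unevenly by arm.

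The reasons matter more than the count. Failing to attend, declining the programme and having a group cancelled can occur only in the arm that is offered the programme straight away. Over the same 15 months no control parent had to turn up to anything in order to stay in. Leaving such parents out compares intervention parents who started the programme with nearly all controls, whether or not those controls would have started. That selection reaches every outcome, and imputation cannot repair it for parents who are outside the dataset. Elsewhere (Dosage) the article treats attendance as a measure of dose. On that footing, zero sessions is the lowest dose and no reason to leave the sample.

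**Working it through.** **1. Participant flow.**
- Intervention losses: 2 + 7 + 2 + 3 = 14, and 180 − 14 = 166.
- Control losses: 142 − 2 = 140.
- Final sample: 166 + 140 = 306. The article's figures are reproduced exactly.

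**2. Loss by arm.**
- Intervention 14/180 = 7.8%; control 2/142 = 1.4%. The difference is 6.4 percentage points and the ratio 5.5. Fisher's exact p = 0.009.
- Without the two judged ineligible: 12/180 = 6.7% v 1.4%, p = 0.026.
- Both p-values ignore clustering by centre and are only descriptive.

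**3. Losses tied to the programme.** 7 (no session) + 3 (group cancelled) + 2 (declined) = 12 of 14. Of the other two, one was excluded for social anxiety, which is not among the listed exclusions.

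**4. Possible bias from analysing the 306.** Assume that the lost parents of both arms would have scored g SD worse at 15 months than those retained. The documents give no value for g, so a range is shown. Net bias = g × (14/180 − 2/142) = g × 0.0637.

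| g (SD) | net bias (SD) |
|---|---|
| 0.2 | 0.013 |
| 0.4 | 0.025 |
| 0.8 | 0.051 |
| 1.0 | 0.064 |

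If the lost parents would have scored better, the sign reverses.

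**5. Dilution and power.** Power Analyses uses 0.40 SD, 80% power, 5% significance (two-sided assumed), design effect 1.30 and 10% attrition.
- Its figures are reproduced: about 100 per arm, × 1.30 = 130, and 130/0.90 = 144.
- If the effect is 0.40 SD in the 166 and zero in the 14, the effect by allocation is 0.40 × 166/180 = 0.369 SD.
- Effective sizes for 180 v 142 are 180 × 0.90/1.30 = 124.6 and 142 × 0.90/1.30 = 98.3.
- Standard error of the difference = √(1/124.6 + 1/98.3) = 0.135.

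| Set | Effect (SD) | Power |
|---|---|---|
| 166 v 140 | 0.40 | 0.83 |
| 180 v 142 | 0.40 | 0.84 |
| 180 v 142 | 0.369 | 0.78 |

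**The case against.** The strongest reply is that no sentence limits the primary analysis to the 306. The phrase about the final sample stands in an account of recruitment, the analysis section plans imputation, and the analysis set may be defined in a document not shown. This stands in part: it cannot be asserted that the trial's primary analysis departs from allocation. But the article does more than stay silent. It fixes 306 as both the final sample and the number recruited, and nothing in it brings the 16 back.

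It can also be said that the article describes the 16 as having withdrawn and calls only two of them excluded. Whether the others refused further assessment is not stated. For the non-attenders and the three whose group was cancelled, the reasons given concern sessions, not data collection.

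A reader might infer four stronger points that the documents do not support:

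- **That the effect is shown to be overstated.** No baseline or outcome data on the 16 are given, and the direction in step 4 depends on an assumption.
- **That power falls to about 74%.** That pairs 0.369 SD with the planned 100 effective parents per arm. The set recommended here is 180 v 142, for which power is about 78%. Power Analyses also does not say whether 0.40 SD already allows for non-attenders.
- **That the age criterion was applied unevenly,** because one child was too young while the sample shows "age range = 17.2–36.4 months". The same sentence gives 176 boys as 54.6%, but 176/306 = 57.5% and 176/322 = 54.7%. The toddler figures may describe all 322, or the count may be a misprint. The excluded child could itself be the 17.2-month minimum.
- **That the article contradicts its own statement** "The study will follow the CONSORT guidelines for intervention evaluation". The article does not set out what those guidelines require of an analysis set, and it does report losses and reasons by arm.

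**Conclusion.** The point holds in conditional form. The counts are exact, the losses follow allocation, and at least 12 of the 14 intervention losses come from not taking up or not being offered the programme. If the 306 are analysed, as the text indicates, the comparison is not by allocation and is open to selection in one arm.

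The likely size is modest: about 0.01 to 0.06 SD against 0.40 SD, for assumed deficits of 0.2 to 1.0 SD equal in both arms. If the 14 gain nothing, the effect by allocation is about 0.37 SD. A small expected bias does not justify giving up the randomised comparison when it can be kept at little cost. The set should be fixed before outcomes are analysed, since choosing it afterwards would look driven by the data.

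Separately from any assumption, 306 recruited with baseline questionnaires cannot be reconciled with 322 enrolled with baseline questionnaires.

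**What to change.** 1. State that the primary analysis includes all 322 parents in the arm their centre was allocated to (180 v 142). Use any 15-month data obtained from the 16. Handle what is missing by the planned multiple imputation or by likelihood, using the baseline questionnaires.
2. Say how this works for observed outcomes. Baseline observations exist only for the randomly selected dyads (246 in the Results), so the baseline available for all 322 is the questionnaire.
3. Leave a parent out of the analysis as ineligible only on a listed criterion that could be judged before allocation, applied in the same way to both arms. This governs the analysis set, not who is offered the programme.
4. Report the 306-parent analysis as a sensitivity analysis.
5. Correct the abstract and Trial Status to agree with the 322 in the Results.

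The cost is wording and a corrected flow statement; no new data are required. The estimated effect may be slightly smaller. If no follow-up exists for the 16, the result will rest on the assumption that, given baseline, they resemble the retained parents. The report should say so.
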